## Abstract

**Background:**

Patients with schizophrenia are characterized by high prevalence rates and chronicity that often leads to long-term institutionalization. Under the traditional medical model, treatment usually emphasizes the management of psychotic symptoms through medication, even though anti-psychotic drugs are associated with severe side effects, which can diminish patients’ physical and psychological well-being. Tai-chi, a mind-body exercise rooted in Eastern health philosophy, emphasizes the motor coordination and relaxation. With these potential benefits, a randomized controlled trial (RCT) is planned to investigate the effects of Tai-chi intervention on the cognitive and motor deficits characteristic of patients with schizophrenia.

**Methods/design:**

A 3-arm RCT with waitlist control design will be used in this study. One hundred and fifty three participants will be randomized into (i) Tai-chi, (ii) exercise or (iii) waitlist control groups. Participants in both the Tai-chi and exercise groups will receive 12-weeks of specific intervention, in addition to the standard medication and care received by the waitlist control group. The exercise group will serve as a comparison, to delineate any unique benefits of Tai-chi that are independent of moderate aerobic exercise. All three groups will undergo three assessment phases: (i) at baseline, (ii) at 12 weeks (post-intervention), and (iii) at 24 weeks (maintenance). All participants will be assessed in terms of symptom management, motor coordination, memory, daily living function, and stress levels based on self-perceived responses and a physiological marker.

**Discussion:**

Based on a promising pilot study conducted prior to this RCT, subjects in the Tai-chi intervention group are expected to be protected against deterioration of motor coordination and interpersonal functioning. They are also expected to have better symptoms management and lower stress level than the other treatment groups.

**Trial registration:**

The trail has been registered in the Clinical Trials Center of the University of Hong Kong (HKCTR-1453).

## Background

### Effectiveness of exercise interventions in psychiatric disorders

The traditional medical model of schizophrenia prioritizes self-care and management of symptoms and functional abilities, both in daily patient care and in research; physical and psychological well-being are considered secondary treatment goals. Patients with schizophrenia have comparatively shorter life expectancies than the general population. This is thought to be due to physical factors (such as higher rates of cardiovascular and metabolic diseases, including obesity) as well as psychological factors (i.e. depression and suicidality) [1–4]. However, these outcomes may be partially attributable to the side effects of medication and poor lifestyle factors such as high-fat low-fiber diets, heavy smoking or a lack of exercise [5]. Hence, the promotion of physical and psychological well-being through exercise is likely to be of benefit to patients with schizophrenia.

Exercise is known to be of psychosocial benefit to patients. Levin and Gimino [6] showed that aerobic exercise reduces depression, anxiety and obsessive-compulsive symptoms in hospitalized patients with schizophrenia, relative to non-exercise-based treatment regimes. Similar interventions have been shown to improve mood, anxiety, depression, self-esteem, energy, concentration, quality of life and social interactions in a range of psychopathological disorders [7, 8]. A 10-week exercise program implemented by Faulkner and Sparkes was found to reduce auditory hallucinations, raise self-esteem and improve sleep patterns as well as general behaviors in patients with schizophrenia [9]. More recent research has uncovered anatomical changes associated with aerobic exercise, most notably increases in hippocampal volume [10], that may improve short-term memory in participants with schizophrenia. In addition to symptom-related outcomes, a lack of physical activity was associated with poorer health-related quality of life indices [11].

### Multiple benefits of Tai-chi as a physical and mental exercise

Based on Eastern health philosophies which focus on the interrelatedness of body and mind, Tai-chi is a form of moderate aerobic exercise that places emphasis on mental well-being [12, 13]. The basic principles of Tai-chi center on physical relaxation, mental alertness, movement sequencing and coordination [14]. In targeting the mind and body, Tai-chi may be particularly beneficial in patients with mental illnesses: there is now an increasing body of empirical evidence demonstrating its physical and mental benefits in clinical populations suffering from depression, posttraumatic stress disorders and traumatic brain injury [15–17]. The multiple benefits of Tai-chi were established in a recent review of 42 RCTs on Tai-chi [12]. Tai-chi was found to improve cardiovascular fitness, bone health, motor coordination, balance, flexibility, and to prevent falls [12, 18, 19]. Immunity, a crucial factor in physical health associated with illness prevention and prognosis, also improved after Tai-chi [20]. Furthermore, it was shown to facilitate psychological focus and relaxation [21], and to alleviate mood disturbances, anxiety, stress, tension, depression, anger and fatigue [16].

In addition to alleviating symptoms, Tai-chi can be used to target motor and cognitive deficits [22], which are subtle manifestations of cerebellar abnormalities and changes in neurological pathways [23]. Psychotropic drugs often induce severe motor deficits, including parkinsonism, dyskinesia and akathisia. Problems in movement and memory can potentially be alleviated by the practice of Tai-chi. The strength of the Wu-style (Cheng form) of Tai-chi [24] is its emphasis on rhythm and coordination. Participants name each movement while practicing; this process demands attention, concentration, memory and physical exertion within the exercise routine. Continual practice is highly encouraged after the completion of classes.

Despite efforts to investigate the impact of Tai-chi on psychological health outcomes, only one study has been published on the effectiveness of Tai-chi in schizophrenia. This study, conducted over 12 weeks, reported a reduction in negative symptoms in patients who had practiced Tai-chi [25]. It is postulated that the focus required for Tai-Chi encourages identification with the inner self, allowing problems of dissociation and attention, characteristic of schizophrenia, to be addressed. Nonetheless, little is known about the specific cognitive benefits of Tai-chi, or of the possible physiological mechanisms involved.

### Schizophrenic Symptoms and the HPA Axis

Salivary cortisol, a neuroendocrine indicator of stress and immunity, can provide insight into the possible physiological mechanisms underlying schizophrenia [16]. Patients with schizophrenia tend to have altered cortisol levels and stress responses, though studies conducted thus far have demonstrated both hyper- and hypo-function of the hypothalamic–pituitary–adrenal (HPA) axis which regulates cortisol levels [26]. Abnormally blunted cortisol responses have also been recorded in patients with schizophrenia [27]. Both hyper- and hypo-activity of the HPA axis have adverse effects on physical and psychological health. For patients with schizophrenia, increased cortisol levels are associated with more severe negative symptoms [28] and worse cognitive functioning in terms of verbal memory [29]; blunted cortisol responses are also associated with poorer quality of life [30]. While a previous study has demonstrated the effectiveness of Tai-chi in lowering salivary cortisol concentrations [31], the effects of lowered cortisol concentrations on symptoms, and other physical and psychological deficits that impair patient well-being, are virtually unknown. Alleviation of symptoms, other deficiencies and psychological health challenges can benefit patients’ overall functioning and quality of life. Tai-chi has been shown to confer these benefits in a number of chronic conditions [32].

### Research objectives

The present study protocol aims to explore the effects of Tai-chi on the symptoms (both positive and negative), motor and cognitive deficits (in terms of motor coordination, motor sequencing and memory), general functional disabilities, stress and salivary cortisol levels in patients with schizophrenia. The effectiveness of Tai-chi practice will be compared to an alternative exercise regimen and a waitlist control group.

## Methods/design

A non-blind, 3-arm randomized controlled trial (RCT) with waitlist control design will be used. Eligible participants will be randomized into (i) Tai-chi, (ii) exercise or (iii) waitlist control groups, on a 1:1:1 basis. The research is conducted in compliance with the Helsinki Declaration, and ethical approval has been obtained from Institutional Review Board of the University of Hong Kong/ Hospital Authority Hong Kong West Cluster (Ref: UW 11–481) before participant recruitment and randomization take place. Human Research Ethics Committee for Non-Clinical Faculties of the University of Hong Kong.

The exercise control will serve as a comparison to delineate the unique benefits of Tai-chi that cannot be accounted for by similar levels of moderate aerobic exercise. This comparison will facilitate a deeper understanding of the positive benefits of Tai-chi, such as attainment of mental tranquility and relaxation, which cannot be explained by physical exercise alone. While exercise is known to confer stress-reducing benefits, there are few studies that compare Tai-chi with alternative exercise interventions [33].

The waitlist control group will continue to receive regular medication and care during the intervention phase. Participants in this group will be offered the Tai-chi or exercise classes on a voluntary basis following completion of the study. Three assessment phases will be carried out for all groups at three time points: (i) baseline, (ii) 12th week (post-intervention time-point), and (iii) 24th week (maintenance time-point).

Figure 1 illustrates the treatment received by the intervention group, the waitlist control condition received by the control group, and the data collection points of the study.

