### Intervention

The Tai-chi intervention is based on the first segment of the Wu-style Cheng-form Tai-chi chuan, comprising 22 simple movements [24]. The basic principal of this form is the emphasis on attention and coordination. Learning the names of each move will promote concentration and focus during practice. Results from the pilot study were used to optimize this program, to maximize learning and memory of the movements while encouraging practice. This will involve the use of flash cards with descriptive diagrams of the movement forms. The intervention will be conducted by mental health professionals with formal training in Tai-chi, who have attended 12 training sessions for instructors at the professional Tsui Woon Kwong Tai-chi Institute.

To design a control exercise regime of comparable intensity, a pilot control study was conducted with four schizophrenic patients (two male and two female) with former Tai-chi experience. The patients’ heart rates were measured by a portable heart rate monitor while they practiced a full set of Tai-chi movements. Based on the data collected, a qualified fitness instructor then devised a moderate aerobic exercise routine designed to achieve 50–60% maximal oxygen consumption (VO_2 max_) for the exercise group. The 1-hour exercise intervention, to be led by mental health professionals, will include a warm up, stretching and joint movements (15 minutes), walking (10 minutes), stepping (10 minutes), mild weight training (10 minutes) and cool down stretching (15 minutes).

For both the Tai-chi and exercise groups, a 1-hour weekly class will be held for 12 consecutive weeks. Sessions will be conducted in groups of 20. Participants will also be invited to a 45-minute, twice-weekly training session under the guidance of mental health professionals in between trainer-led classes. The waitlist group will receive routine care and be offered a similar Tai-chi or exercise class after the 24-week assessment period.

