### Setting

All assessment and interventions will be conducted in a residential long-term care hostel for psychiatric patients in Hong Kong.

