### Instruments

The PANSS is a psychiatric rating system that will be used to assess the positive and negative symptoms of schizophrenia exhibited in the week prior to assessment. It is based on information from the reports of family members or primary care staff, as well as a 40-minute semi-structured psychiatric interview with the patient. The patient will then be rated on a scale of 1 to 7 on 30 different symptoms pertaining to 3 different subscales—positive, negative, and general psychopathology—with internal consistency rats ranging from 0.73 to 0.83.

Assessments will be conducted by trained researchers using the following devices:*Psychiatric Symptoms - The Positive and Negative Syndrome Scale (PANSS 30)* [34]*Motor Coordination and Sequencing – Neurological Evaluation Scale (NES)* [35]2.1Motor Coordination Subscale: motor coordination will be measured using four tasks, including (i) tandem walk, (ii) rapid alternation movements, (iii) finger/thumb opposition, and the finger-to-nose test [36]. The ability of the patient to perform each of the above tasks will be rated on a 3-point scale based on the number of mistakes.2.2Sequencing of Complex Motor Acts Subscale: this will consist of four tasks associated with the sequencing of motor acts, including (i) the fist-ring test (right and left hands), (ii) the fist-edge-palm test (right and left hands), (iii) the Ozeretski test, and (iv) the rhythm tapping test [36]. Performance will be rated on a 3-point scale based on the number of mistakes.

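### The trial is declared non-blind with no exception for outcome assessors, which leaves the PANSS and, to a lesser degree, the NES open to avoidable detection bias

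*Protocol article*

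**What the plan says.** Methods/design sets the blinding status in one sentence: "A non-blind, 3-arm randomized controlled trial (RCT) with waitlist control design will be used". No other section masks the assessors or says that masking them is infeasible.

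Instruments names who assesses: "Assessments will be conducted by trained researchers using the following devices". The list includes the PANSS, with 30 symptoms each rated from 1 to 7. Besides an interview with the patient, the rating uses informants: "It is based on information from the reports of family members or primary care staff". It also includes two NES motor subscales, for which the section says of the sequencing tasks: "Performance will be rated on a 3-point scale based on the number of mistakes". The coordination tasks are scored in the same way.

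Intervention names a different role for delivery. For Tai-chi: "The intervention will be conducted by mental health professionals with formal training in Tai-chi". For exercise: "The 1-hour exercise intervention, to be led by mental health professionals".

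Setting places everything in one building: "All assessment and interventions will be conducted in a residential long-term care hostel for psychiatric patients in Hong Kong".

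The Abstract, under Discussion, records what the team expects: "subjects in the Tai-chi intervention group are expected to be protected against deterioration of motor coordination and interpersonal functioning". It goes on to expect better symptom control and less stress than in the other groups.

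**The concern.** Residents and class leaders cannot be blinded to Tai-chi. Assessors can be, at least in principle. Two of the domains in which the team expects Tai-chi to win, symptoms and motor coordination, are scored by observers, and the plan does not keep the allocation from them. If an assessor knows the arm and shares the expectation, part of a measured difference on the PANSS or NES may come from the scoring.

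The exercise arm does not guard against this. It is there to isolate what Tai-chi adds beyond moderate aerobic activity. It matches activity, but it does not stop a rater from scoring the two active arms differently. A difference between two active arms may also be small, so a modest rating shift would matter most there.

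Baseline is exposed too. As Participant recruitment is worded, residents are randomized first and baseline assessment is then arranged, at least a week before classes start. The arm can therefore be known at all three phases, and adjustment for baseline cannot be relied on to remove the bias.

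**Working it through.** **1. Which outcomes are exposed**

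| Outcome | How it is scored (Instruments; Analysis of salivary cortisol) | Room for assessor expectation |
|---|---|---|
| PANSS | Rater judgement, 1 to 7, from interview and informants | Most |
| NES subscales | Observer, 3 points, tied to mistakes made | Some, less than PANSS |
| Digit span | Repetition of digit strings | Little |
| Lawton IADL, PSS | IADL self-report; PSS the participant's own rating | Little; masking assessors would not protect them |
| Salivary cortisol | Laboratory assay | Little |

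The concern is therefore mainly about the PANSS, with the NES second.

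**2. Who rates and who leads classes**

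Instruments says trained researchers; Intervention says mental health professionals. The different role names suggest different people, but no section says so. Masking therefore looks feasible, by inference.

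**3. How large the effect could be (illustration)**

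The document gives no figure for rating bias, so there is no plan figure to reproduce.

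Inputs from the protocol article:
- 153 participants, allocated 1:1:1, so 153/3 = 51 per arm.
- About 25% attrition, so 51 × 0.75 = 38.25, taken as 38 per arm.
- Two-sided significance level 0.05.

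Assumptions not in the document: no true effect, a rating shift b of 0.1 or 0.2 SD towards Tai-chi, and a two-sample t-test of Tai-chi against one comparator.

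Formula: noncentrality δ = b × √(n/2), with 2n − 2 degrees of freedom. The rejection rate is P(|T| > critical value), where T is noncentral t with parameter δ.

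| n per arm | b | δ | Rejection rate |
|---|---|---|---|
| 38 | 0 | 0 | 5.0% |
| 38 | 0.1 | 0.1 × √19 = 0.436 | 7.1% |
| 38 | 0.2 | 0.2 × √19 = 0.872 | 13.8% |
| 51 | 0 | 0 | 5.0% |
| 51 | 0.1 | 0.1 × √25.5 = 0.505 | 7.9% |
| 51 | 0.2 | 0.2 × √25.5 = 1.010 | 17.0% |

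A larger sample makes this worse, because a fixed bias does not shrink as the standard error does.

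**4. Why these rates do not carry over to the planned test**

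Data analysis plans a repeated-measures ANOVA over three arms and three times.
- A shift that is equal at every phase cancels in the group-by-time term.
- A shift that appears only after baseline does not cancel. For a change between two phases with equal variances and within-person correlation ρ, the shift in SD units of change is b/√(2(1 − ρ)). That equals b at ρ = 0.5, is larger above 0.5 and smaller below. The document does not give ρ.
- With raters unmasked at baseline, a shift there could either offset or add to a later one, depending on its direction.

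The table shows only that a small shift can matter at this sample size.

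**The case against.** The strongest reply is that non-blind is a label which does not say whose blinding is meant. Read narrowly, it fits a trial in which participants and instructors know the arm, and a condensed article may leave assessor staffing to the full protocol. Part of this stands: the document never says outright that raters will be told the allocation. But the label is a stated design choice applied to the whole trial, with no exception for assessors. A fuller document that masked them would have to qualify it.

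Four further objections limit the point, and all of them stand:

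- **Separate raters.** A reader might infer that raters and class leaders are certainly different people, so that masking needs no extra staff. The document supports only different role names. A trained research assistant obtains consent on site, and whether that person also handles allocation or rates outcomes is not stated.
- **Informants.** A reader might infer that class leaders also serve as PANSS informants. The document names family members or primary care staff and does not link them to the classes.
- **Scope.** A reader might extend the point to every outcome. Digit span, the self-report scales and cortisol would gain little from masked assessors, so the expectation of lower stress is largely untouched. NES scoring leaves less room for expectation than the PANSS.
- **Feasibility.** Classes, guided practice and assessments share one hostel, and the PANSS needs a long interview plus informant reports. Some unmasking is likely, so an assessor-blind label could claim more than is achieved.

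**Conclusion.** The point holds for the PANSS and, to a lesser degree, the NES. Followed as written, the plan allows assessors to know the arm while they score domains in which the team expects Tai-chi to win. This affects both comparisons, including Tai-chi versus exercise, which is meant to show a unique benefit.

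The size is unknown. It may be tempting to read the 7%–17% range as this trial's type I error rate. The document does not support that: the shift is assumed, and the test is not the planned one. The conclusion rests on two things: that the non-blind declaration extends to assessors, which is its natural reading, and that masking is feasible, which is inferred from the role names. It is a worthwhile improvement to the conduct of the trial and does not show that the results would be wrong.

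**What to change.** 1. Withhold the allocation from the researchers who rate the PANSS and NES at baseline, week 12 and week 24.
2. Use raters who neither lead classes nor handle allocation.
3. Ask residents and staff not to disclose the arm at assessments.
4. Where possible, take PANSS informant reports from staff who do not lead that resident's class.
5. Record each rater's guess of the arm.
6. Describe the trial as assessor-blind for the PANSS and NES only if these steps are taken. If they are not, state why, and interpret both outcomes as open to detection bias.

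**Cost:** no added participants or patient procedures, and no change to the target of 153. Expect scheduling constraints and some accidental unmasking in a single hostel. Whether extra staff are needed depends on who now rates and who handles allocation, which the article does not say.

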**Figure 1 Fig1:**
[figure not shown]
**Flow diagram of intervention/waitlist control and data collection points.**

### Participant recruitment

Patients diagnosed with chronic schizophrenia, residing in a Hong Kong mental health rehabilitation complex providing both long-term care and halfway house services will be recruited to the study. Patients will be invited to participate by their respective social workers, based on specific inclusion and exclusion criteria.

Inclusion criteria will be as follows: a) fulfillment of DSM-IV TR criteria for schizophrenia, or diagnosis by a psychiatrist, b) age between 18 and 65 years, c) ability to understand and speak Cantonese, and d) no formal training in or regular practice of Tai-chi.

Exclusion criteria will be as follows: a) diagnosis of acute schizophrenia requiring hospitalization, b) presence of unstable or severe schizophrenic symptoms (e.g. persistent withdrawal) that would limit ability to interact or participate in the class, c) history of brain trauma or organic mental disorders (e.g. mental retardation or dementia), d) presence of physical disabilities, e) presence of other severe illnesses which may impair cognitive or visuo-motor function, cause physical pain or limit life expectancy to 10 years or less.

In determining the sample size, we have taken into consideration multiple independent variables, using multiple regression modeling with a medium effect size (f^2^) of 0.15, at 0.8 power and a significance level of 0.05. Experimental, clinical and demographic variables anticipated to affect the intervention outcome were included in the model. An attrition rate of approximately 25% is expected, based on prior community trials of Tai-chi interventions in elderly patients, and exercise programs for patients with severe mental illnesses [33]. Thus, a total of 153 participants will be targeted for the study.

Upon application of inclusion and exclusion criteria, a trained research assistant will obtain informed consent from participants at the rehabilitation complex. Eligible and consenting participants will then be randomized into one of the three treatment conditions, and baseline data collection will be arranged at least one week prior to the commencement of group programs.

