### Data analysis

#### Effectiveness of the Tai-Chi intervention

Repeated measures analysis of variance using SPSS software will be used to explore the effectiveness of the Tai-chi intervention over the three assessment time points, relative to the exercise and waitlist control groups. Ordinary least squares (OLS) regression will be used to assess the relationship between the dependent variables (outcomes) and independent variables (covariates). A model of the role of Tai-chi with respect to other influencing variables, such as clinical prognosis or frequency of practice, will deepen understanding of the true effects of Tai-chi in this clinical population. All levels of significance will be set at p < 0.05. Intention-to-treat analysis will be used to prevent participant selection bias due to study discontinuation.

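### The 0.8 power belongs to a multi-predictor regression test, not to Tai-chi versus exercise, Tai-chi versus waitlist, or the planned repeated measures ANOVA

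*Protocol article*

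**What the plan says.** All the sizing inputs stand in the protocol article under Participant recruitment. The basis is "we have taken into consideration multiple independent variables, using multiple regression modeling with a medium effect size", with a "medium effect size (f^2^) of 0.15" "at 0.8 power and a significance level of 0.05". On the content of the model it says: "Experimental, clinical and demographic variables anticipated to affect the intervention outcome were included in the model". It continues "An attrition rate of approximately 25% is expected", and concludes that "a total of 153 participants will be targeted for the study". The paragraph names no contrast between arms, no outcome and no time point for the 0.8.

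The introductory paragraphs of Methods/design set 1:1:1 allocation to Tai-chi, exercise or waitlist and give the purpose of the active comparator: "The exercise control will serve as a comparison to delineate the unique benefits of Tai-chi". Under Effectiveness of the Tai-Chi intervention, the effect is examined by repeated measures ANOVA over three time points, "relative to the exercise and waitlist control groups". Ordinary least squares regression appears there too, but for relating outcomes to covariates.

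**The concern.** A power statement is useful only if it is tied to the hypothesis that the trial tests. Here the 0.8 attaches to a regression in which arm is one set of terms among several. A joint test of all the terms has the same power whether the explained variance comes from arm or entirely from age, illness duration and medication. It can reach 80% while Tai-chi does nothing.

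The effectiveness question is about differences between arms and is to be answered by a different analysis. A reader who takes 0.8 at a medium effect as the power for Tai-chi against exercise could read a null result there as good evidence of no unique benefit. That comparison is between two active programmes, where a modest difference is plausible and a null result is easily over-read.

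**Working it through.** **Inputs from the protocol article.** f² = 0.15, which is R² = 0.15/1.15 = 0.13; power 0.8; alpha 0.05; attrition about 25%; total 153; allocation 1:1:1. So 153/3 = 51 are randomised per arm, and 153 × 0.75 = 114.75 complete, about 38 per arm.

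**Inputs assumed.** The number of predictors p, scanned from 1 to 15; standardised differences d of 0.4 to 0.6; a two-sided test for pairwise comparisons; baseline correlations of 0.3 to 0.7.

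**Step 1: reproduce 153.** For a joint F test of p predictors, the noncentrality is λ = f² × N with p and N − p − 1 degrees of freedom. Find the smallest N with power of at least 0.8, then divide by 0.75.

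| Predictors tested jointly | Completers needed | After 25% attrition |
|---|---|---|
| 8 | 109 | 146 |
| 9 | 114 | 152 |
| 10 | 118 | 158 |
| 11 | 123 | 164 |

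Nine predictors give 152, and the next multiple of three is 153. Power for that joint test is 80.4% at 114 completers (λ = 0.15 × 114 = 17.1) and 80.9% at 115.

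**Step 2: try a treatment-only test at the same f².** With 1 df, 55 completers are needed, and 55/0.75 = 73.3, so 74. With 2 df (three arms), 68 are needed, and 68/0.75 = 90.7, so 91. Neither leads to 153.

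**Step 3: what 153 offers for one pairwise comparison, as an illustration.** Two-sample t test at one time point, no adjustment, two-sided 0.05, noncentrality d × √(n/2), n per arm:

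| d | Power, n = 38 | Power, n = 51 |
|---|---|---|
| 0.4 | 41% | 52% |
| 0.5 | 58% | 71% |
| 0.6 | 73% | 85% |

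At n = 38, 80% power needs d = 0.651. The figures are the same for Tai-chi versus waitlist, because the arms are equal in size.

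**Step 4: baseline adjustment.** Adjustment multiplies the residual SD by √(1 − r²), where r is the correlation between baseline and follow-up. The article gives no r. At n = 38:

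| Assumed r | √(1 − r²) | Power at d = 0.5 | d for 80% power (0.651 × factor) |
|---|---|---|---|
| 0.3 | 0.954 | 62% | 0.62 |
| 0.5 | 0.866 | 70% | 0.56 |
| 0.6 | 0.800 | 77% | 0.52 |
| 0.7 | 0.714 | 85% | 0.46 |

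**The case against.** **The arithmetic is sound, and the paragraph never claims 0.8 power for Tai-chi versus exercise.** Both are true. 153 follows from its inputs under a reasonable predictor count, so this is not a calculation error. What stands is that the only power figure offered for a trial of effectiveness describes something other than a difference between arms.

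**A reader might infer that only an overall test of exactly 9 predictors gives 153.** That is too strong. The count is back-solved. Nine terms tested as a block inside a model of 11, 13 or 15 predictors also need 114 completers. Ten predictors need 118, which fits 153 if attrition is 1 − 118/153 = 22.9%, and the article says only approximately 25%. All of these are still multi-term tests, so the conclusion does not depend on which was used. Nor is this a test of covariates alone: experimental variables are in the model.

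**A reader might also infer that the trial has 58% power.** The documents do not support that. The value d = 0.5 appears nowhere in them, and an unadjusted completer t test is not the planned analysis. If f² = 0.15 described the two-arm contrast itself, then d = 2 × √0.15 = 0.77 and power at 38 per arm would be about 92%; but 153 would then not follow from the inputs. Using both follow-ups could also help. With equal correlations r and a sustained effect, the baseline-adjusted mean of the two follow-ups has relative variance (1 + r)/2 − r², which is 0.56 at r = 0.3 and 0.44 at r = 0.6. Power at d = 0.5 is then about 82% and 90%. Clustering within classes of 20 and multiple outcomes would pull the other way. The illustration shows that the 0.8 does not carry over; it does not settle the power of the planned analysis.

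**Tai-chi versus exercise is not ranked above Tai-chi versus waitlist.** Correct: Research objectives names both. The point applies equally to each.

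**A condensed article may leave the predictor count to the full protocol.** Fair, and its absence alone would be no finding. The point is that the stated power is attached to a quantity that is not the effect under study.

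**Conclusion.** The point holds. The 0.8 at f² = 0.15 is power for a regression test in which experimental, clinical and demographic variables act together. It is not power for Tai-chi against either comparator, nor for the repeated measures ANOVA. The identification is an inference, because the predictor count is not stated, but it is well supported: about 9 jointly tested predictors give 153, and treatment-only tests give 74 or 91.

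The size of the gap depends on assumptions that the article does not fix. For an unadjusted completer comparison at one time point, 80% power needs d of about 0.65. At d = 0.5, power is 58%, or 71% if all 51 per arm are analysed. With baseline adjustment at 38 per arm it is 62% to 85% over correlations of 0.3 to 0.7. The plan cannot claim a figure in that range without stating its correlation. None of this shows that 153 is too few; it shows that the stated power does not say whether it is enough.

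**What to change.** Keep 153 and rewrite the sample size paragraph under Participant recruitment to do three things:

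1. Say that the 0.8 at f² = 0.15 refers to the joint regression test, and give the number of predictors used. The sponsor should confirm this from the original calculation.
2. Add the detectable difference for Tai-chi versus exercise, and for Tai-chi versus waitlist, at 51 randomised and about 38 analysed per arm: d of about 0.65 with 80% power, two-sided 0.05, unadjusted at one time point.
3. If a baseline-adjusted figure is wanted, show it as a range over stated assumed correlations (0.62, 0.56, 0.52 and 0.46 for r = 0.3, 0.5, 0.6 and 0.7), not as a single value.

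The cost is one paragraph and a stated figure that looks less favourable. No extra participants and no change to trial conduct are needed.
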